### Equipment, intervention, outcome measures and study procedure

#### Robot

We selected the ChARMin (Children’s Arm Rehabilitation Mechatronic Interface) device that was developed in a collaboration between the Sensory-Motor Systems Lab (Federal Institute of Technology Zurich, Switzerland) and the Swiss Children's Rehab [32]. ChARMin (Fig. 2) is an actuated exoskeleton robot, which can actively support joint movements of the shoulder, elbow, forearm and wrist for the left or the right arm. To support the patient’s movements, the motors compensate the weight and friction of the robot arm and can provide guidance force. Therapists can adjust the guidance from a non-supporting mode, where the robot transparently follows the patient’s movement, to a fully supported mode. This allows adapting the physical support of ChARMin to each patient during therapies. However, for the planned pilot study, participants will not receive physical guidance or support of the device; the motors will only compensate for the weight and friction of the robot.

**Fig. 2 Fig2:**
[figure not shown]
The ChARMin robot. The ChARMin exoskeleton: a young boy practicing with ChARMin’s small distal module

ChARMin includes a small and large distal module to fit the anthropometrics from about 5-year-old children to adolescents. Interfaced with different exergames, it provides and facilitates playful training of arm and hand functions, especially for children with more severe upper limb impairments. During the execution of the exergames, different sensors and game parameters are recorded and processed to extract the assessment measures (e.g. number of velocity peaks, precision on the target or reaction time).

#### Intervention

We selected an exergame for the pilot study that is based on the Quality of Movement assessment provided by ChARMin [33]. The participants will need to perform goal-directed reaching movements. The participants will have to steer an avatar, which represents the position of the participant’s hand, on the screen by moving the upper extremity with the attached exoskeleton towards one of eight targets appearing in random order radially around the centre. The children will be instructed to reach the targets by the most direct path and as fast as possible. The avatar will need to remain on the target for 2 s. After that, the target will disappear. Then, the centre object will reappear, and the avatar will have to be moved back to the centre object to remain there for another 2 s before the next target will appear. If the participant will not reach the target within 10 s, it will disappear, and the centre object will reappear.

Since interference levels must be appropriate to produce a contrast between random and blocked schedules [34], we developed two versions of the exergame; one can be played in the transversal plane, the other in the frontal plane (i.e. the two versions of the exergames have different spatial characteristics, which should require different motor programmes) [11].

Choosing different varying characteristics would be an option, and has already been evaluated [35]. Including variations based on different motor programmes has been suggested to create a more difficult learning situation [11]. As we did not want to increase the learning difficulty too much for the participants, we decided to vary the tasks only in one parameter. In the transversal plane version, the exergame will be displayed as a horizontal plane on the screen. The participant will move inside a haptic wall, i.e. the movement will be restricted mechanically to a horizontal plane, which will be located 10 cm below the shoulder joint for the small and the large distal module (Fig. 3(A1 and A2)). Mainly horizontal shoulder adduction and abduction, and elbow flexion and extension will be required to play the horizontal version of the exergame. In the frontal plane version, the exergame will be displayed vertically on the screen. Here, the participant will move inside a haptic wall located 30 cm in front of the shoulder joint for the small distal module and 35 cm in front of the shoulder joint for the large distal module (Fig. 3(B1 and B2)). Shoulder flexion and extension, (horizontal) abduction and adduction, shoulder internal- and external rotation and some elbow flexion and extension will be required to play the vertical version of the exergame.

**Fig. 3 Fig3:**
[figure not shown]
Restrictions of movement inside a haptic wall on the horizontal (A) and the vertical plane (B). The movement area during the horizontal plane exergame with the small distal module (A1) and the large distal module (A2). The haptic wall is located 10 cm below the shoulder joint. The movement area on the vertical plane is located 30 cm in front of the shoulder joint for the small distal module (B1) and 35 cm in front of the shoulder joint for the large distal module (B2)

To motivate the participants to perform a large number of repetitions actively, we developed different avatar-target-exergame-scenarios (Fig. 4). Prior to the exergame, the participant will select his/her own avatar to improve compliance. For the transversal plane exergame version, the avatar will either be a unicorn who will be eating cupcakes (targets) or a snail eating apples. For the frontal plane exergame, the avatar will be an UFO landing on planets or a submarine collecting fish. As previously mentioned, we will instruct the participants to ‘move the unicorn/snail/UFO/submarine to the cupcake/apple/planet/fish as direct and fast as possible’.

**Fig. 4 Fig4:**
[figure not shown]
ChARMin exergames. Upper row: transversal version of the ChARMin exergames (A1: avatar unicorn, target cupcake; A2: avatar snail, target apple). Lower row: frontal version of the ChARMin exergames (B1: avatar UFO, target planet; B2: avatar submarine, target fish, in this picture the gold target is displayed)

Reaching a target will be rewarded with a score displayed in the middle of the screen. The score will be calculated using the time remaining to reach the target (0 to 10 s), and the distance to path ratio (1 = direct movement to the target):
$$ \mathrm{Score}=\mathrm{time}\ \mathrm{remaining}+\left(11-\frac{\mathrm{path}}{\mathrm{distance}}\right) $$

Therefore, the maximum score for each target will be 20. A randomly chosen target out of the eight targets per trial will be a golden target with a value worth five times as much to increase the participant’s motivation. The current score of the ongoing trial will be displayed in the left upper corner of the screen. The total score will be displayed after each trial and will not exceed 240 points.

The blocked group will play 15 trials of one version (i.e. in either the horizontal or vertical plane) followed by 15 trials of the other version. The order of the two blocks will be randomised and the same for all the practice sessions for the same participant. The random group will play the 30 trials of the two versions in a pseudo-random order. The only restriction will be that the same version cannot be repeated more than twice in a row.

To generate observable changes due to motor learning, a large number of repetitions (i.e. hundreds of daily repetitions for upper extremity movements) will be required [36, 37]. Results from a recent study proposed changes in performance scores during three sessions, each lasting 20–25 min of robot-assisted arm training, and showed that movements were repeated more than 3000 times [38]. Yet, it is challenging to define the number of repetitions sufficient to induce motor learning, while maintaining an acceptable length of sessions to keep the burden for the participants at a minimum and their motivation at a maximal level. In our study, participants will perform 16 reaching movements within one trial of exergames. Over the three sessions (30 trials per session), this would lead to 1440 repetitions of the reaching movement. We consider that this number will induce change due to motor learning. On the other hand, we expect a maximum session duration of 120 min, which seems acceptable.

When switching between the two exergame versions, the therapist will not need to adjust the hardware settings, but she will need to choose the appropriate version of the exergame on the interface. In order to have the same conditions for all participants, we will renounce using the support modalities of the robot. While children with unilaterally affected upper limb function will practice and perform all the assessments with their more affected side, children with bilaterally affected upper limb function will use the arm which they subjectively use more in daily life.

#### Outcome measures

##### Outcomes of the main study

***Primary outcome: immediate transfer of the practiced skill*** We chose the Melbourne Assessment 2 subscale fluency (MA2_fluency_) as the primary outcome measure for the immediate transfer. The MA2 consists of the four subscales movement range, accuracy, dexterity and fluency [39] and is an adequate measurement for research and clinical use in children with cerebral palsy [40]. The intraclass correlation coefficient of the test-retest reliability of the MA2_fluency_ is 0.96 (95% confidence interval 0.90–0.99), the minimal detectable change is 2 points and the minimal clinically important difference is at least 3 points [40]. Concerning the concurrent validity, Pearson’s correlation coefficients between the MA2_fluency_ and other tests amounted to 0.67 (Bruininks-Oseretsky Test of Motor Proficiency, Second Edition, subtest 3, manual dexterity), 0.76 (Box and Blocks Test) and 0.40 (Paediatric Motor Activity Log–Revised, quality of movement) [40]. The responsiveness of the MA2_fluency_ is high, which is indicated by significant change scores and a high standardised response mean value of 1.84 [40].

From a clinical point of view and in line with literature (e.g. [9]), we consider the transfer to be an important aspect of learning. We hypothesise that MA2_fluency_ will improve when practicing the reaching movements. During the exergames, the participant will be instructed to reach the target by the most direct path, i.e. as fast as possible. This is in line with the MA2_fluency_ scoring criteria, which include jerkiness, tremor and/or reduced speed of movement [41].

Since we considered the MA2_fluency_ to be more sensitive to change instantly after the practice sessions due to the relatively short practice period and to avoid a potential loss to follow-up at later time points, we chose the immediate transfer as the time point of interest for the primary outcome.

One of three trained occupational therapists will score the MA2_fluency_ by analysing the video. The rater will be blinded for the participant’s group allocation, the time point of assessment and the randomisation code. The sum scores will be calculated and used for further analysis.

***Secondary outcomes***
*Delayed transfers*: The delayed transfers (1 day and 1 week after the last practice session) will be determined by the sum score of the MA2_fluency_ at these time points.

*Immediate and delayed retentions*: To evaluate whether the participants can retain what they have learned, the so-called exergame test will be performed. It consists of one block of three trials of the horizontal version of the exergame and one block of three trials of the vertical version of the exergame. Although the order of the versions will be randomised between the participants, it will remain the same within each participant throughout the study.

With these exergame tests, we anticipated measuring the construct ‘movement fluency’. There is no generally accepted way of quantifying fluency. Several studies have used the absolute number of velocity peaks of a single movement [42, 43]. Yet, as we also wanted to take into account the length of the movement path, we will calculate the parameter ‘number of peaks’, which is the number of velocity peaks (i.e. when the difference between a local speed minimum and a local speed maximum exceeds a value of 2.5% of the measured maximal speed) normalised to the covered distance of the movement path (nP_norm_). We will calculate nP_norm_ for each movement (i.e. one value from the centre to the target and one for the return to the centre starting point) that will lead to 16 data points per trial. The parameter nP_norm_ has shown reliable results during the Quality of Movement assessment [33], on which the exergames are based. In a comparable group of 23 participants, the parameter nP_norm_ showed no systematic error between two measurements within 3 to 7 days, an intraclass correlation coefficient of 0.94, a percentage standard error of measurement (divided by the grand mean) of 6.4% and a percentage smallest real difference (divided by the grand mean) of 17.7% (unpublished data).

*Acquisition*: To observe motor learning during the practice sessions, nP_norm_ will be the parameter of interest too. It will also be recorded 16 times per trial, which will lead to 480 data points per practice session.

##### Feasibility outcomes

In line with recommendations on reporting protocols of pilot and feasibility trials [26], we will apply the following ten specific feasibility criteria:
Are the chosen inclusion criteria specific enough to result in a sample of participants, which is suitable for this pilot study (e.g. are they able to play the exergame)?Is the recruitment rate feasible? Since the main randomised controlled trial would require a large number of participants, it is relevant to know the number of participants that will be recruited during a certain period.The number of children enquired for the study, number of participants recruited, number of complete datasets within 1 year will be recorded and used to calculate recruitment rates.Is the scheduling procedure feasible? The appointments will be planned for 3 weeks for each participant. The person conducting the exergame tests and the MA2_fluency_ always will need to be the same. The same will apply for the person instructing the child during the practice sessions. Absences of personnel (e.g. due to illness, holidays or part-time employment) and the children (e.g. due to illness or short-term planned medical appointments), as well as the availability of the robot and material for the MA2_fluency_ (i.e. whether they are not used for therapy at the time points of the measurements), will need to be considered. Information about whether it is possible to schedule rooms, persons involved and the robot and table for performing assessments will be noted.Is the randomisation procedure feasible? Experiences of the persons involved will be collected and evaluated to answer this question.Is the whole procedure feasible for the participants? The rather time-consuming procedure and the high number of repetitions might be difficult for at least some of the participants because of fatigue or lack of motivation to play the exergames so many times. Both reasons influence motor learning negatively. Therefore, it is important to determine whether the participants included in this study are able to comply the whole study procedure. Information about aborted or shortened sessions or other incidents and their reasons (e.g. pain or discomfort, fatigue) will be taken from the lab journal.Is the handling of the robot feasible? The ChARMin robot has been in use in the clinical and research area since 2015. Since it is a newly developed tool, it is important to evaluate its handling. Any technical issues will be noted and then retrieved from the lab journal.Is the handling of the large amount of data feasible? Information from the assessors and the analyst on the primary outcome will be used.Are the outcome measures responsive and sensitive enough within this setting? Responsiveness analysis of the assessment data will be performed.Is there a confounding influence of parallel therapies within the rehabilitation setting? As the study will be conducted during the inpatient rehabilitation stay, it is important to estimate whether parallel-applied therapies could confound the results. Since an additional control group following usual care would require a larger sample, we chose a design in which each participant acts as its own control and, therefore, we included control measurements during the first week of the study procedure.The changes in the outcomes between week 1 (control week) and week 2 (practice week) will be compared. The kind and number of additional therapies taking place during the different study periods will be recorded to increase the quality of reporting [44].Is it feasible to conduct the main trial with respect to the needed sample size calculated from the data obtained for the primary motor learning outcome? With the data of the primary outcome measure, we will calculate the required sample size for the main trial.

#### Study procedures

The study procedure is shown in Fig. 1 (SPIRIT Figure) and Fig. 5.

**Fig. 5 Fig5:**
[figure not shown]
Study procedure. The study duration for each participant is 3 weeks. Week 1 contains the familiarisation of the two versions of the exergame, two assessment blocks (Melbourne Assessment 2 and exergame tests) and the Test of Nonverbal Intelligence, Fourth edition (TONI-4). The TONI-4 will be planned before the first practice session day (i.e. on appointment 2 or 3). Week 2 contains three practice sessions with an assessment block proceeding the first practice session and another assessment block after the last practice session to evaluate immediate transfer and retention. One day after the last practice session, the assessment block is repeated to assess the delayed one-day transfer and retention). During week 3, the last assessment block is scheduled one week after the last practice session to assess the delayed 1-week transfer and retention. *TONI*-*4* Test of Nonverbal Intelligence, Fourth edition

##### Week 1

During the first appointment, the setup of the robot and the adjustments according to the child’s anthropometrics will be performed. This takes approximately 15 min. Each participant will then become familiarised with the two versions of the exergame. First, the transversal version ‘Unicorn’ will be played with manual guidance and verbal support from the therapist. Then, the transversal version ‘Snail’ will be played with only verbal guidance of the therapist. The same procedure will be followed for the exergame that is played in the frontal plane (i.e. ‘Submarine’ will be played with manual guidance and verbal support followed by ‘UFO’, which will be played with only verbal support). Subsequently, an assessment block consisting of the MA2_fluency_ [45] and an exergame test will be performed.

During week 1, also all the parameters for randomisation by minimisation will be obtained from the participant’s medical history (e.g. age, gender, diagnosis), from the attending occupational therapist (MACS level), and trained neuropsychologist (TONI-4). Participants will be characterised by age, gender, weight, height, diagnosis (including information about the affected side and specific features such as spasticity, dyskinesia or mixed condition) and the MACS level. After obtaining the minimisation parameters, participants will be allocated to their group.

##### Week 2

On each of three consecutive days, all participants will practice 30 trials (15 trials of the horizontal and 15 of the vertical version of the exergame) in either a blocked or random order (according to their group allocation). Right before the first and after the last practice session, an assessment block will take place to assess the acquisition and immediate transfer and retention. One day after the last practice session, the assessment block will be repeated (1 day delayed transfer and retention).

##### Week 3

One week after the last training session, the assessment block will be repeated (1 week delayed transfer and retention).

The first session will include robot set-up and familiarisation and will be scheduled for approximately 75 min. Assessment blocks will take approximately 35 min and practice sessions 60 to 90 min. As the duration of an exergame trial depends on the child’s performance, it will vary largely and will affect the overall duration of the practice session. Once the robot settings have been adjusted to the participants’ anthropometrics, no additional set up time will be required. We defined an upper time limit of 120 min per session, which could be reached during practice sessions 1 and 3 that will also include a previous or subsequent assessment block. Sessions will be aborted after 120 min.

##### Standardisation and blinding

All the appointments will be scheduled during the same half of the day throughout the 3 weeks to reduce the influence of daytime on the outcome (e.g. fatigue increasing throughout the day, the severity of spasticity changing over the day, etc.). A trained physiotherapist or human movement scientist will conduct the practice sessions and the assessments following standardised instructions. The same person will conduct at least all assessment blocks with a participant and, whenever possible, also the practice sessions. In each session, an assistant will note irregularities and support the therapist.

While the assessor of the primary outcome (video analysis of the MA2_fluency_) will be blinded to the participants’ allocation and the time-point of the assessment, the participants will be blinded to the detailed aims of the study. Both will be informed that the intervention will investigate motor learning with new exergames but not about our interest in investigating the effects of different practice orders.

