**Fig. 1 Fig1:**
[figure not shown]
Standard Protocol Items Recommendation for Interventional Trials (SPIRIT) figure. Actions and appointments throughout the whole study. *The test of nonverbal intelligence is conducted before the first practice session (outcome needed for randomisation by minimisation). **Allocation is done when all the parameters for minimisation are obtained; at latest on the day before the first practice session

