### Group allocation

Participants will be allocated to a blocked or random practice group using randomisation by minimisation. This method enables balancing several prognostic factors in small samples [30]. We will impute parameters that potentially influence motor learning. To reduce the risk of selection bias, these factors should be balanced between the groups, even in the case of uneven distribution.

We will use the following minimisation parameters: age (preschool age: 5–6 years, primary school age: 7–12 years, secondary school age and older: 13–18 years); gender (female, male); diagnose (congenital, acquired); manual ability (MACS level I, II, III or IV); and cognitive ability according to the Test of Nonverbal Intelligence–Fourth edition (TONI-4), which evaluates abstract reasoning and problem solving (Index Score < 70: very poor, 70–79: poor, 80–89: below average, 90–110: average, 111–120: above average, 121–130: superior and > 130: very superior) [31]. The minimisation parameters are equally weighted. A study nurse will receive the minimisation parameters of each new participant by one of two researchers involved in recruitment. She will enter the parameters in a custom-written Matlab programme, which will allocate the participant to either the blocked or random order group. The study nurse will be unaware of this definition and the purpose of the study. The study nurse will enter the allocation in a file, which will allow the researcher to schedule the appointments and perform the practice and measurement sessions. The study nurse will not be involved otherwise in this trial. In case the study nurse is unavailable, we will assign another independent person who will perform this procedure.

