##### Primary outcome

***Immediate transfer*** The relative difference $$ \left(\frac{MA{2}_4- MA{2}_3}{MA{2}_3}\right) $$ of the MA2_fluency_ sum score between the time point right before the first practice session (MA2_3_) and the time point immediately after the last practice session (MA2_4_) will be compared between the groups. A *T* test (or Mann-Whitney *U* test, if data are not normally distributed) will be performed.

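### The arm can be known before the primary baseline (MA2_3) is administered, although holding the allocation back until after that assessment would cost almost nothing

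*Protocol article*

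**What the plan says.** All places are in the Methods of the protocol article.

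- **When allocation is made.** Fig. 1 legend: "Allocation is done when all the parameters for minimisation are obtained; at latest on the day before the first practice session". Study procedures, Week 1, agrees: "After obtaining the minimisation parameters, participants will be allocated to their group".
- **Who receives it.** Under Group allocation, the study nurse enters the result in a file, "which will allow the researcher to schedule the appointments and perform the practice and measurement sessions".
- **When the primary outcome is measured.** Study procedures, Week 2: "Right before the first and after the last practice session, an assessment block will take place". The primary analysis takes the relative change in the MA2 fluency sum score "between the time point right before the first practice session" (MA2_3) and the point immediately after the last one (MA2_4).
- **Who administers.** Standardisation and blinding: "A trained physiotherapist or human movement scientist will conduct the practice sessions and the assessments following standardised instructions". It continues: "The same person will conduct at least all assessment blocks with a participant and, whenever possible, also the practice sessions". During practice the therapist sees the order, because at each switch "she will need to choose the appropriate version of the exergame on the interface" (Intervention).
- **Who is blinded.** The occupational therapist who rates the video does not know group, time point or randomisation code, and the participants do not know the detailed aims. No one else is described as blinded.

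**The concern.** Blinded video rating protects the score from the rater's expectations. It cannot undo what happened in front of the camera. MA2 fluency is scored partly on speed of movement, so the way a child is prompted, paced or encouraged can change what the rater sees. If the person doing this knows the arm, the baseline is no longer guaranteed to be independent of it, although it is measured before any practice.

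At stake is the between-group difference in change. It supplies the reported 95% confidence interval for the primary outcome and the difference of means in the sample-size formula for the main trial.

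**Working it through.** The point concerns sequence, so the main check is to put the steps in order.

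1. The minimisation parameters are complete once the TONI-4 is done, on appointment 2 or 3 (Fig. 5 legend).
2. Allocation is made, at the latest the day before practice session 1 (Fig. 1 legend).
3. The result goes into the file meant for the researcher (Group allocation).
4. MA2_3 and the exergame test are administered just before practice session 1 (Week 2).
5. Practice runs over three consecutive days.
6. MA2_4 and the exergame test are administered just after the last practice session.

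Steps 4 and 6, the two ends of the primary change score, both follow step 3. Nothing in the article holds the file closed between steps 3 and 4. The first week-1 assessment block precedes allocation, and the second may do so, but neither enters the primary change score.

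**Is early release needed?** Recruitment says that appointments are scheduled when consent is given, before allocation. Both arms then have the same practice days, the same assessment blocks and 30 trials per session (Week 2). The arm first matters when practice trial 1 starts.

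**Scale of a possible effect.** The article gives no operator effect, so what follows is illustration. Let b3 and b4 be the arm-dependent shifts at MA2_3 and MA2_4. The bias in the absolute between-arm change is b4 − b3.

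- A shift of 1 point at one time point only gives a bias of 1 point in size. Against the stated minimal detectable change this is 1/2 = 0.5, and against the minimal clinically important difference of at least 3 points it is at most 1/3 = 0.33.
- On the planned relative scale, assume a true change from 10 to 12: (12 − 10)/10 = 20%. A baseline shift of +1 gives (12 − 11)/11 = 9%; a shift of −1 gives (12 − 9)/9 = 33%.
- An equal shift of +1 at both points gives an absolute change of 13 − 11 = 2, unchanged, and a relative change of 2/11 = 18% instead of 20%. It cancels fully on the absolute scale and largely on the relative one.

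**Effect on main-trial planning.** The article's formula is n = (1.96 + 0.84)² × 2σ²/(μ1 − μ2)² = 15.68 × σ²/(μ1 − μ2)² per group. The SD of change is not given; 2 to 4 points are assumed, with a true difference of 2 points. Adding 1 point of bias in the direction of the effect makes the difference 3 points.

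| Assumed SD | n per group, difference 2 | n per group, difference 3 |
|---|---|---|
| 2 | 15.68 × 4/4, so 16 | 15.68 × 4/9, so 7 |
| 3 | 15.68 × 9/4, so 36 | 15.68 × 9/9, so 16 |
| 4 | 15.68 × 16/4, so 63 | 15.68 × 16/9, so 28 |

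**Against sampling error.** With 10 per group the half-width of the 95% interval is 1.96 × SD × √(2/10): 1.75, 2.63 and 3.51 points for SD 2, 3 and 4. Imprecision therefore exceeds an assumed bias of 1 point throughout this range.

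**The case against.** Several stronger readings are tempting, and the article does not support them.

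- **That the primary outcome is assessed unblinded.** Only administration is open. Scoring is blinded to arm and time point, instructions are standardised, and an assistant notes irregularities.
- **That someone who knows the arm runs every assessment.** At least the first week-1 block precedes allocation. Using one person for practice as well is only a preference, and Feasibility outcomes fixes the assessor and the practice instructor as two separate requirements. The Fig. 1 legend also dates when allocation is done, not when it is read; earlier knowledge is a fair inference from Group allocation, but it remains an inference.
- **That the administrator knows the hypothesis and would favour one arm.** The article states only what raters and participants are told, and the Discussion says it is not known which order is better. No direction of bias is shown.
- **That the exergame test is equally exposed.** It is scored from robot sensors in a fixed game without physical guidance. Verbal encouragement could still matter, but there is less room for it.
- **That the protocol contradicts itself.** It declares a single-blinded study, so this is a design weakness.

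Two further arguments carry weight. First, this is a feasibility pilot that tests hypotheses only if power suffices, and its imprecision is larger than any bias assumed here. Second, if the same person handled a child identically at both time points, b3 and b4 would cancel, and protecting MA2_3 alone would leave b4 uncancelled. This limits what the change can promise: it reduces the net bias when the two shifts point in opposite directions or when b3 is more than twice b4, and not otherwise. What it does secure is a baseline that cannot depend on the arm, with the remaining exposure confined to the post-practice assessments, where it can be declared.

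**Conclusion.** The point holds in a limited form. The primary baseline and its exergame test are administered after the arm can be known, and no section blinds the administrator. Blinded rating, standardised instructions and the assistant reduce the risk without removing it.

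No size can be given. The 1-point shift, the baseline of 10 and the SDs of 2 to 4 are assumptions that show scale only, and they are not evidence that any bias will occur. The conclusion rests on the stated order of events and on the inference that the researcher may read the allocation file once it is filled. The change is worth making because early release serves no need visible in the article and because the pilot is meant to settle how the main trial is run.

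**What to change.** 1. **Hold the result back.** The study nurse may run the minimisation as soon as the parameters are complete, but the result is released to the researcher only after the pre-practice assessment block (MA2_3 and exergame test) on practice day 1 is finished. Say so in the Fig. 1 legend, in Group allocation and in Study procedures, Week 1.
2. **State the remaining limitation.** MA2_4 and the delayed assessments are administered by someone who may know the arm, and a shift at these points would not be offset by the baseline.
3. **Optional.** Where existing staff allow, a person unaware of the arm could run a child's assessment blocks. This trades against operator continuity and staffing, which the article already treats as a feasibility question, so it is a choice for the sponsor and not a correction.

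**Cost.** For item 1, the file is opened about 35 minutes into practice day 1, and the practice order is set up then. Time that day is already tight: 35 minutes of assessment plus 60 to 90 minutes of practice makes 95 to 125 minutes against the stated limit of 120. Preparing the sequences for both arms beforehand would avoid using more of it. Item 2 costs one sentence.
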